### Relevant concomitant care permitted or prohibited during the trial {11d}

Patients randomised to the rehabilitation programme will be asked not to start any new paramedical interventions between the start of the study and the end of the intervention, for example not initiating additional psychological interventions or starting with aerobic activities outside the rehabilitation programme. By imposing these restrictions, adherence to the protocol (i.e. 6-week rest, whereafter the rehabilitation programme will start) can be guaranteed.

### Provisions for post-trial care {30}

This study does not provide post-trial care. There is no anticipated harm for trial participation and consequently no compensation for anticipated harm.

### Outcomes {12}

At baseline, all outcomes will be evaluated. Afterwards, patients undergo a SCS trial period, followed by IPG implantation in case of a successful trial period (50% pain reduction and 50% reduction in pain medication use, according to the current Belgium reimbursement rules). Six weeks after the IPG implantation, the second assessment will take place. Follow-up assessments will be performed directly after the intervention of 14 weeks (immediate effects, short-term primary endpoint) and 3 months (short-term effects), 6 months (mid-term effects) and 12 months (long-term effects, long-term primary endpoint) after the intervention. The assessment directly after the intervention of 14 weeks will serve as the short-term primary endpoint, while the assessment at 12 months after the intervention serves as the long-term primary endpoint. To prevent test order effects, the test order of the self-reported measures will be randomised for each individual patient, at each assessment. At the 3-month visit, no actigraphy will be registered. During the other follow-up visit, all outcome measurements will be evaluated. Figure 1 presents the project flowchart.

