### Trial design {8}

OPERA is a two-arm, parallel-group multicentre randomised controlled trial evaluating whether the work ability in PSPS-T2 patients after SCS implantation is different after a personalised biopsychosocial rehabilitation programme specifically targeting RTW, compared to usual care (difference design). Patients will be randomised (1:1) to (a) a personalised biopsychosocial RTW rehabilitation programme of 14 weeks or (b) a usual care arm, both with a follow-up period of 12 months after the intervention.

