#### Primary outcome

The ‘Work Ability Index’ (WAI) will be used as the primary outcome measure, which measures the work ability taking into account physical and mental parts of work as well as different diseases and their impact on work ability [44]. More specifically, the WAI consists of a questionnaire with 10 questions concerning current work ability compared with the lifetime best, work ability in relation to the job demands, number of current diseases diagnosed by a physician, estimated work impairment due to diseases, sick leave, self-prognosis of work ability and mental resources [45]. The total score of the WAI has a range from 7 to 49 with higher scores indicating higher work ability. This total score can further on be divided into four categories of work ability: poor (score from 7 to 27), moderate (score from 28 to 36), good (score from 3 to 43) and excellent (score from 44 to 49) [46].

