### Sample size {14}

Sample size calculation was performed using G*Power version 3.1.9.2 for evaluating differences in work ability between both interventions (the control and experimental intervention). Based on the least favourable design (two treatment arms, in which patients are measured three times) with a small effect size (*η*^2^=0.069; *d*=0.28) [66], a sample size of 112 patients is needed to reach a significant between-subject effect. This sample size calculation accounts for a 20% loss to follow-up after 1 year and for a SCS trial failure rate of 11.3%, according to Belgian reimbursement rules [5]. Calculations were based on two-tailed testing (alpha=0.05) with 85% power. Allocation ratio (N2/N1) was defined as 1, resulting in 110.3 patients (56 patients in the experimental group and 56 in the control group (*N*=112)).

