## Statistical methods

### Statistical methods for primary and secondary outcomes {20a}

Longitudinal mixed models will be used to evaluate and compare therapy effects. The primary outcome will be analysed as the difference in WAI score from baseline to the short-term primary endpoint immediately after the intervention and to the long-term primary endpoint at 12 months after the intervention (taking into account the longitudinal nature of the trial) between both groups. Baseline variables will be used as covariates. A similar strategy will be applied for secondary outcome measurements. The threshold for statistical significance will be set at *p*<0.05. Statistical as well as clinically significant differences will be defined, and the effect size will be determined.

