## Discussion

The OPERA study will evaluate whether a multidisciplinary biopsychosocial approach for improving RTW is different from usual care in terms of work ability for patients with PSPS-T2 after SCS implantation. This allows us to tackle the high burden of patients that are not re-entering the labour market by proceeding towards a personalised multidisciplinary evidence-based conservative intervention for a costly and debilitating condition. If the new intervention, consisting of a personalised biopsychosocial RTW rehabilitation programme, is more effective than the usual care alone for improving work ability in PSPS-T2 patients after SCS implantation, then the new therapy should be applied as the new standard conservative treatment for these patients. Therefore, this project holds the potential to have utilisation goals for several stakeholders among which patients themselves to improve their work ability, health professionals since new treatment guidelines could be developed based on the results of this project and the health security system since the study findings may allow for scientifically evidence-based decision-making, in order to decrease expenses of the public and private health security systems accompanied by PSPS-T2 patients with SCS that are not resuming work.

Furthermore, these study findings could open avenues for similar studies evaluating the benefits of this multidisciplinary programme in patients after failed surgery, where RTW is currently not achieved (i.e. interdisciplinary rehabilitation programme after surgery as such). Hence, the project has the potential to significantly impact upon the progress of science and clinical practice in the field of “failed surgery” (i.e. applicability for other patient groups in whom RTW is not achieved). The awareness is growing that the burden of PSPS-T2 on our society is expected to increase over time due to the annual increase of spinal surgeries [72], but innovative and methodologically rigorous trials exploring the potential to decrease the socio-economic burden are essentially lacking.

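### Two primary WAI time points share one p<0.05 threshold with no order, alpha split or success rule; if either suffices, the two-sided error is about 9%, not 5%

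*Protocol article*

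**What the plan says.** Primary outcome: "The ‘Work Ability Index’ (WAI) will be used as the primary outcome measure".

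Outcomes {12} gives this measure two primary time points. The assessment directly after the programme "will serve as the short-term primary endpoint, while the assessment at 12 months after the intervention serves as the long-term primary endpoint".

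Statistical methods {20a} uses longitudinal mixed models: "The primary outcome will be analysed as the difference in WAI score from baseline to the short-term primary endpoint immediately after the intervention". The same sentence goes on to the 12-month endpoint. One general threshold follows: "The threshold for statistical significance will be set at *p*<0.05".

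Sample size {14} sizes the trial for one between-subject effect: "Calculations were based on two-tailed testing (alpha=0.05) with 85% power". Trial design {8} likewise frames the question as one of a difference between arms.

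Multiple testing appears only in the additional analyses {20b}, for correlations between changes in ability and the secondary measures. No interim analysis is planned, so alpha is not spent elsewhere.

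The Discussion states the consequence of success. If the programme is more effective for work ability, "then the new therapy should be applied as the new standard conservative treatment for these patients". It names no time point.

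**The concern.** Two primary endpoints, one unadjusted threshold and one adoption conclusion do not fit together unless a rule links them. The article gives none. If a positive result at either time point would be taken as success, the trial has two chances to reach its headline conclusion, and the nominal 5% no longer describes the risk of error for that conclusion.

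A split result has no conclusion fixed in advance under the text as printed. The programme might help at its end and show nothing at 12 months, or the reverse. For a return-to-work intervention, whether the effect lasts is central, so this should not be settled after the data are seen.

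**Working it through.** **Inputs.** Two primary WAI contrasts (Outcomes {12}, {20a}). Threshold 0.05 ({20a}), two-tailed ({14}). The correlation r between the two test statistics is not given, so it is an assumption and is varied from 0 to 0.9. The calculation also assumes a separate test at each time point and that success on either is enough.

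**Reproducing the plan's sample size.** This shows what the 0.05 was spent on.
- η² = 0.069 gives f = √(0.069/0.931) = 0.272.
- Between-subject effect in a repeated-measures ANOVA with 2 groups and 3 measurements. The correlation among measurements is not stated; 0.5 is assumed. Noncentrality is λ = N·f²·3/(1 + 2×0.5).
- With N = 84, λ = 84 × 0.0741 × 3/2 = 9.34 and power at alpha 0.05 is 85.5%. With N = 82 it is 84.7%, so 84 is the smallest even number that reaches 85%.
- 84 × (1 + 0.20 + 0.113) = 110.3, rounded to 112. This matches the article.

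The stated size therefore corresponds to one test at two-sided 0.05, not to two primary tests.

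**False findings when either endpoint suffices.** Under no effect at either time point, treat the two statistics as bivariate normal with correlation r.
- A difference in either direction: P = 1 − P(|Z₁| ≤ 1.96 and |Z₂| ≤ 1.96). At r = 0 this is 1 − 0.95² = 9.75%.
- A false claim of benefit: P = 1 − P(Z₁ ≤ 1.96 and Z₂ ≤ 1.96). At r = 0 this is 1 − 0.975² = 4.94%.

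| Assumed r | Any difference, two-sided | Claim of benefit only |
|---|---|---|
| 0 | 9.75% | 4.9% |
| 0.3 | 9.5% | 4.8% |
| 0.5 | 9.1% | 4.5% |
| 0.7 | 8.3% | 4.2% |
| 0.8 | 7.8% | 3.9% |
| 0.9 | 7.0% | 3.5% |
| One test, for comparison | 5% | 2.5% |

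A simulation with 2 million draws at r = 0.5 gave 9.1% and 4.5%.

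**After a rule is fixed.**
- Fixed sequence: the second test is reached only if the first rejects, so with no effect at either time point the chance of any false finding is that of the first test, 5%.
- Both must succeed: at most 5%, with no split.
- Alpha 0.025 for each: 4.9% two-sided at r = 0 and 4.65% at r = 0.5.

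**Power at 0.025.** For the plan's own between-subject effect with 84 evaluable patients, power falls from 85.5% to 77.9%. Regaining 85% takes 100 evaluable patients, and 100 × 1.313 = 131.3, about 132 enrolled instead of 112.

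**The case against.** **A reader might infer a 9% chance of wrongly declaring the programme better.** The documents do not support that. Testing is two-tailed, so half of the 9% consists of findings that the programme is worse. The figure for a false claim of benefit is about 4.5%, against 2.5% for a single test. The relative inflation is the same.

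**Separate tests and an either-endpoint rule are not stated.** This is correct. {20a} mentions the longitudinal nature of the trial, and {14} powers one overall effect. A single joint or overall group test would not inflate the error, and neither would a rule that both endpoints must succeed. The Discussion is prose, not a decision rule. Two separate contrasts are the more natural reading of {20a}, but the percentages remain conditional on it. If both must succeed, the cost moves to power: were each contrast powered at 85%, both would succeed with probability 0.85² = 72% at r = 0 and 81% at r = 0.9. {14} does not mention such a requirement.

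**The endpoints are labelled short-term and long-term, so they may be two separate claims, each with its own 5%.** That would be defensible if the conclusions were kept apart. The Discussion draws one conclusion about work ability without a time point.

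**The statistical analysis plan may settle the order.** It may, and it is not shown. But the article is not merely silent. It declares two primaries, sets one threshold for them, confines multiplicity to the correlations and states what success would lead to. What it fixes is incomplete for its own conclusion.

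**Conclusion.** The point holds in conditional form. The article names two primary endpoints under one p<0.05 threshold and gives no order, split or success rule. If each has its own test and either suffices for the adoption conclusion, the chance of a false finding of a difference in either direction is about 9%, not 5%. That figure takes a test correlation of about 0.5; over 0.9 down to 0 the range is 7.0% to 9.75%. The chance of a false claim of benefit is about 4.5% (3.5% to 4.9%), not 2.5%.

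The correlation, the separate tests and the either-endpoint rule are all assumptions. A reader might go further and say that the plan commits itself to the inflated error. It does not: the text neither adopts nor excludes the either-endpoint reading. What does not depend on these assumptions is that the article fixes no conclusion for a split result.

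**What to change.** In {20a}, before unblinding, state a fixed sequence. Test the between-group WAI contrast directly after the intervention at two-sided 0.05, and test the 12-month contrast at two-sided 0.05 only if the first is significant. The sponsor may reverse the order. Describe the other time points as supportive, and say in the Discussion which result the adoption statement rests on.

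The cost is a sentence or two and no extra patients. The price is that the second endpoint cannot be claimed if the first fails.

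Holm's procedure is an alternative that does not impose an order, but its first step is at 0.025. At that level, power for the plan's own between-subject effect drops from about 85% to about 78% with 84 evaluable patients, assuming a correlation of 0.5 among the repeated measurements. If a joint test or a both-must-succeed rule was intended, writing that down also closes the gap; for the latter, the power in {14} should be restated for both endpoints together.

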**Fig. 1 Fig1:**
[figure not shown]
Project flowchart. Participant timeline. Abbreviations. IPG implantable pulse generator, *n* number, RTW return to work, SCS spinal cord stimulation, T time

#### Primary outcome

The ‘Work Ability Index’ (WAI) will be used as the primary outcome measure, which measures the work ability taking into account physical and mental parts of work as well as different diseases and their impact on work ability [44]. More specifically, the WAI consists of a questionnaire with 10 questions concerning current work ability compared with the lifetime best, work ability in relation to the job demands, number of current diseases diagnosed by a physician, estimated work impairment due to diseases, sick leave, self-prognosis of work ability and mental resources [45]. The total score of the WAI has a range from 7 to 49 with higher scores indicating higher work ability. This total score can further on be divided into four categories of work ability: poor (score from 7 to 27), moderate (score from 28 to 36), good (score from 3 to 43) and excellent (score from 44 to 49) [46].

#### Secondary outcome measurements

##### Functional capacity evaluation 

Functional capacity evaluations are commonly used for making fitness-for-work decisions and facilitating the RTW process [47]. An objective evaluation of the functional capacity will be performed by a shortened version of the Isernhagen Work Systems (now called WorkWell) functional capacity evaluation protocol. This functional capacity evaluation tool has already been used in chronic low back pain patients with acceptable test-retest reliability [48]. For this specific group of patients, a set of functional assessments that covers the seven basic postures and three lifting tasks will be applied. More specifically, the following tests are performed: standing tolerance, sitting tolerance, kneeling, crouching, forward bending, carrying, stair walking, repetitive sideways reaching, pulling, pushing, lifting low, lifting high and the 6-min walking test.

##### Work status and participation

The Work Rehabilitation Questionnaire (WORQ) will be used to measure work status and participation, which is a reliable questionnaire to evaluate functioning in vocational rehabilitation, based on the International Classification of Functioning, Disability and Health [49]. The information gained when using WORQ contributes to improving interdisciplinary understanding of the patient’s situation and therefore supports the integrative planning of the RTW process or engagement in gainful employment [50].

##### Pain intensity

The visual analogue scale (VAS-100 mm) will be used for the assessment of overall pain, defined as a combination of back and leg pain (but not pain from other body parts). The VAS pain score is believed to be reliable, valid and sensitive to change [51, 52].

##### Health-related quality of life

To describe the health-related quality of life, the EuroQol with 5 dimensions and 5 levels (EQ5D-5L) will be used [53]. Patients subjectively tick the box of the most appropriate statement in each of the 5 dimensions namely mobility, self-care, usual activities, pain/discomfort and anxiety/depression. The EQ5D-5L index scores range from −0.42 to 1, with 0 and 1 corresponding respectively to death and full health, based on preference-weighted health state classification algorithms [54]. Negative values denote health states perceived worse than death. Belgian population norms are available for the EQ5D-5L [55].

##### Physical activity and functional disability

In line with the IMMPACT recommendations for the assessment of physical activity in chronic pain clinical trials [56], actigraphy will be used to objectively capture continuous physical activity and rest/activity cycles in all patients [57]. Recordings will be made by an Actigraph device (ActiGraph, Pensacola, FL, USA). This device will be worn for 1 week after each study visit (except for the 3-month visit).

The Oswestry disability index (ODI) is used to measure functional disability due to abnormalities of the spine [58]. It contains ten topics whereby each topic is scored on a scale from 0 (no disability) to 5 (maximum disability possible). Higher values represent more disability.

##### Sleep quality

Perceived sleep quality will be measured with the Pittsburgh Sleep Quality Index (PSQI). The PSQI is by far the most widely used assessment of subjective sleep quality and contains 7 different sleep-related components: sleep quality, latency, duration, habitual sleep efficiency, sleep disturbance, use of hypnotics and daytime functioning [59].

##### Kinesiophobia

The Tampa Scale for Kinesiophobia (TSK) consists of 17 items to evaluate kinesiophobia in patients with low back pain [60]. Higher scores indicate a higher degree of kinesiophobia. The clinimetric properties are well-established in patients with low back pain [61].

##### Healthcare expenditure

The intervention is expected to have consequences on health-seeking behaviour, based on a previous reporting of pain education in low back pain patients [62]. As patients will learn how to handle their pain better, it is believed that their outreach for healthcare services will be lower with maintaining their quality of life. This will be measured by self-reporting methods (week diaries during the intervention, questionnaires at all other visits). Hence, healthcare expenditure includes hospitalizations and any kind of post-SCS treatment and consultations (e.g. pain killers, physiotherapy, psychotherapy, osteopathy).

##### Anxiety and depression

The Hospital Anxiety and Depression Scale (HADS) aims to measure symptoms of anxiety and depression and consists of 14 items: seven items for the anxiety subscale (HADS Anxiety) and seven for the depression subscale (HADS Depression). Each item is scored on a response scale with four alternatives ranging between 0 and 3. After adjusting for six items that are reversed scored, all responses are summed to obtain the two subscales. Recommended cut-off scores are 8–10 for doubtful cases and ≥ 11 for definite cases [63]. The HADS was found to perform well in assessing the symptom severity of anxiety disorders and depression in both somatic, psychiatric and primary care patients and in the general population [64].

##### Patient activation and self-management

Patient activation measure-13 (PAM) is a 13-item instrument to assess self-reported behaviour, knowledge and confidence for self-management of one’s health. The PAM has proven to be a reliable instrument to measure patient activation and self-management [65]. Patients will be divided in 4 levels, going from disengaged with a lack of confidence (level 1) to individuals who maintain their healthy lifestyle and feel confident about their health (level 4).

### Participant timeline {13}

The participant timeline for OPERA is presented in Fig. 2.

**Fig. 2 Fig2:**
[figure not shown]
Participant timeline (SPIRIT). Abbreviations: EQ5D EuroQol with five dimensions and 5 levels, FCE functional capacity evaluation, HADS Hospital Anxiety and Depression Scale, HE healthcare expenditure, ODI Oswestry disability index, PAM patient activation measure-13, post-int post-intervention, PSQI Pittsburgh Sleep Quality Index, RTW return to work, TSK Tampa Scale for Kinesiophobia, VAS visual analogue scale, WAI Work Ability Index, WORQ Work Rehabilitation Questionnaire

### Sample size {14}

Sample size calculation was performed using G*Power version 3.1.9.2 for evaluating differences in work ability between both interventions (the control and experimental intervention). Based on the least favourable design (two treatment arms, in which patients are measured three times) with a small effect size (*η*^2^=0.069; *d*=0.28) [66], a sample size of 112 patients is needed to reach a significant between-subject effect. This sample size calculation accounts for a 20% loss to follow-up after 1 year and for a SCS trial failure rate of 11.3%, according to Belgian reimbursement rules [5]. Calculations were based on two-tailed testing (alpha=0.05) with 85% power. Allocation ratio (N2/N1) was defined as 1, resulting in 110.3 patients (56 patients in the experimental group and 56 in the control group (*N*=112)).

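### The 85% power in Sample size {14} is for a group effect averaged over three measurements, not for the WAI change at the two single visits that are the primary endpoints

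*Protocol article*

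**What the plan says.** Sample size {14} gives the design and the effect tested: "Based on the least favourable design (two treatment arms, in which patients are measured three times", and "a sample size of 112 patients is needed to reach a significant between-subject effect". The inputs are an effect "with a small effect size (*η*^2^=0.069; *d*=0.28" and the statement "Calculations were based on two-tailed testing (alpha=0.05) with 85% power". The total "accounts for a 20% loss to follow-up after 1 year and for a SCS trial failure rate of 11.3" per cent. The result is given as "Allocation ratio (N2/N1) was defined as 1, resulting in 110.3 patients", rounded to 56 per arm. Neither the correlation between measurements nor which three of the six assessments are meant is stated.

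Statistical methods {20a} defines the primary comparison differently: "The primary outcome will be analysed as the difference in WAI score from baseline to the short-term primary endpoint immediately after the intervention". That sentence goes on to add a second contrast of the same kind, comparing the arms on WAI change up to the final assessment one year after the programme. Outcomes {12} names the same two visits as the short-term and long-term primary endpoints. The model is a longitudinal mixed model with unlisted baseline variables as covariates.

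**The concern.** The sample size section and the analysis section describe different effects. A between-subject main effect over three measurements compares the arms on each patient's mean of three values. The primary comparison looks at one visit at a time, as change from baseline. Averaging removes within-patient noise, so at the same effect size the averaged comparison needs fewer patients than an unadjusted comparison at one visit. If the 85% belongs to the averaged effect, a reader of the protocol is given a power figure that neither primary endpoint was sized for. The least-favourable label adds to this by suggesting that the calculation is conservative.

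**Working it through.** **1. Inputs.** From Sample size {14}: η² = 0.069, two arms, three measurements, two-sided alpha 0.05, power 85%, losses of 20% and 11.3%. The correlation ρ is not stated and is inferred in step 2.

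Effect size: f = √(0.069/0.931) = 0.272. For two equal groups d = 2f = 0.544. The printed d of 0.28 is close to f and does not match η² as a Cohen's d.

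**2. Reproducing the plan's figure.** For the between-subject test, λ = f²·N·m/(1 + (m − 1)ρ), with a noncentral F on 1 and N − 2 degrees of freedom. With m = 3, ρ = 0.5 and N = 84, λ = 0.0741 × 84 × 3/2 = 9.34 and power is 85.5%. Then 84 × (1 + 0.20 + 0.113) = 110.29, the printed 110.3.

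Alternatives do not fit:
- ρ = 0.3 gives N = 68, and 68 × 1.313 = 89.3.
- ρ = 0.7 gives N = 100, and 100 × 1.313 = 131.3.
- f = 0.28 at ρ = 0.5 gives N = 80, and 80 × 1.313 = 105.0.
- A true Cohen's d of 0.28 gives N = 308 before any allowance.

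So the 85% is for the average over three measurements, at ρ = 0.5.

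**3. Evaluable patients.** At 12 months: 112 × 0.80 × 0.887 = 79.5, taken as 79. Directly after the intervention the one-year loss need not have occurred in full. With only the SCS trial failures removed, 112 × 0.887 = 99.3, taken as 99. The range for that visit is 79 to 99.

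**4. Power at a single visit.** Two-sample noncentral t with N − 2 degrees of freedom and noncentrality δ·√(N/4), where
- change score: δ = d/√(2(1 − ρ)), which equals d at ρ = 0.5;
- baseline-adjusted: δ = d/√(1 − ρ²), which is 0.544/0.866 = 0.629 at ρ = 0.5.

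Results at ρ = 0.5:

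| Evaluable N | Change score | Baseline-adjusted |
|---|---|---|
| 84 (the plan's target) | 69% | 81% |
| 79 (12 months; lower end, post-intervention) | 67% | 79% |
| 99 (upper end, post-intervention) | 77% | 87% |

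For 85% power at one visit, 124 evaluable patients are needed unadjusted and 94 baseline-adjusted, against 84 in the plan.

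**5. Dependence on the correlation.** At 12 months with N = 79:

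| ρ | Change score | Baseline-adjusted |
|---|---|---|
| 0.3 | 52% | 71% |
| 0.5 | 67% | 79% |
| 0.6 | 76% | 85% |
| 0.7 | 87% | 92% |

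**6. Separating two causes.** Adding the loss rates leaves 79 patients at 12 months, not 84. With 79, even the averaged test has 83%, not 85.5%. At a fixed N = 84, moving from the averaged effect to the single-visit contrast takes power from 85.5% to 81% with baseline adjustment and to 69% without.

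**7. The label.** At f = 0.272 and ρ = 0.5 the between-subject test needs 124, 94, 84 and 74 patients for 1, 2, 3 and 6 measurements. Three measurements are less favourable than six and more favourable than one.

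**The case against.** The strongest reply is that the shortfall is not established. The correlation of 0.5 is back-calculated from the printed total. It says nothing about how strongly baseline WAI actually predicts later WAI. With baseline adjustment and a correlation of about 0.6, power at 12 months is 85%. The planned mixed model takes baseline variables as covariates, so the adjusted figure fits the text better than the change-score figure. The model also keeps patients with partial data, so a two-sample test among completers is only an approximation. All of this stands, and it makes the size of the shortfall conditional. It does not remove the mismatch: the calculation that yields 110.3 tests a different effect and, among the correlations tried, fits only 0.5.

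Four stronger readings are tempting and are not supported:
- A reader might infer that both endpoints have only 67–79% power. That range rests on the full one-year loss and so belongs to the 12-month visit. The post-intervention visit may reach 87% with baseline adjustment.
- A reader might infer that the least-favourable label is simply false. The between-subject test is a demanding choice among repeated-measures tests (the group-by-time interaction needs 28 patients at the same inputs), and three measurements need more patients than six. The label fails only against a single-visit contrast.
- A reader might quote a joint power for success at both visits. The protocol does not say that both must succeed.
- A reader might assume that baseline is one of the three measurements, which would dilute the averaged effect. The protocol does not say which three are meant.

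**Conclusion.** The point holds as a misstatement of what the 85% refers to. It is the power for an effect averaged over three measurements and does not apply to the primary endpoints as {12} and {20a} define them. Under the calculation's own inputs, 12-month power is below 85% both with and without baseline adjustment. At the post-intervention visit it may fall below or above 85%, depending on adjustment and on how many patients remain.

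These figures assume d = 0.544 (the η² reading), a correlation of 0.5, alpha 0.05 at each endpoint and the plan's own loss rates. If the printed 0.28 were a true Cohen's d, 12-month power at N = 79 would be only about 23% (change score) to 29% (adjusted). That conflict is a separate matter, but it has to be settled before any restated power is printed. Part of the 12-month drop comes from the additive loss allowance and not from the choice of effect.

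**What to change.** Keep N = 112. In Sample size {14}:

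1. Reconcile η² = 0.069 with the printed d = 0.28 and state the effect size actually used.
2. Replace the averaged between-subject power with power for the time-specific, baseline-adjusted WAI contrast, given separately for the post-intervention and 12-month endpoints. For each, state the assumed correlation and the evaluable number at that visit. One figure cannot serve both.
3. Remove the least-favourable label, or limit it to the repeated-measures options it was compared with, since a single-visit contrast is less favourable than an average over three measurements.

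The cost is a recalculation and a few sentences, with no extra patients. The downside is that the stated 12-month power becomes less favourable under the calculation's own inputs: about 79% baseline-adjusted at a correlation of 0.5, if the η² reading is confirmed.

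### The sample-size section gives one effect size in two incompatible forms: N = 112 follows from eta-squared 0.069 (d about 0.54), not from the printed d = 0.28

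*Protocol article*

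**What the plan says.** Everything relevant stands in the protocol article, Sample size {14}.

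- Software: "Sample size calculation was performed using G*Power version 3.1.9.2".
- Design: "two treatment arms, in which patients are measured three times".
- Effect size, with a literature citation: "with a small effect size (*η*^2^=0.069; *d*=0.28".
- Target: "a sample size of 112 patients is needed to reach a significant between-subject effect".
- Error rates: "Calculations were based on two-tailed testing (alpha=0.05) with 85% power".
- Losses: the number "accounts for a 20% loss to follow-up after 1 year and for a SCS trial failure rate of 11.3" per cent.
- Result: "Allocation ratio (N2/N1) was defined as 1, resulting in 110.3 patients", rounded to 56 per arm, 112 in total.

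The section gives no correlation between the repeated measurements and no conversion between the two effect-size measures.

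**The concern.** Eta-squared and d appear side by side as two expressions of the same effect. With two arms of equal size one fixes the other, so a reader can convert and check. The conversion fails by a factor of about two in d and about 3.6 in eta-squared.

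The effect size is the main assumption behind the sample size, and it tells the reader what a non-significant result would mean. The words as printed, a small effect of d = 0.28 at 85% power, suggest that a null result would be fairly strong evidence against a small benefit on the Work Ability Index. If the number of patients was derived from an effect about twice as large, the trial cannot support that inference. Anyone who reuses d = 0.28 with N = 112 to plan a later trial would carry the error forward.

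**Working it through.** **Inputs from Sample size {14}:** two arms, 1:1; m = 3 measurements; two-sided alpha 0.05; power 85%; losses of 20% and 11.3%; eta-squared 0.069 or d = 0.28; result 110.3, rounded to 112. **Assumed:** correlation rho between measurements, not given in the document.

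**Step 1. Convert the two effect sizes (no rho needed).** For two equal groups, f = √(η²/(1 − η²)) and d = 2f.

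- From eta-squared 0.069: f = √(0.069/0.931) = 0.272; d = 2 × 0.272 = 0.54.
- From d = 0.28: f = 0.14; η² = 0.0196/1.0196 = 0.019.

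**Step 2. Reproduce the plan's figure.** For the G*Power repeated-measures between-factors test, power comes from a noncentral F with 1 and N − 2 degrees of freedom and λ = N·f²·m/(1 + (m − 1)·rho).

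- With f = 0.272, m = 3, rho = 0.5 and N = 84: λ = 84 × 0.0741 × 3/2 = 9.34, power 85.5%. N = 82 gives 84.7%, so 84 is the smallest total in equal arms that reaches 85%.
- Adding the two loss rates: 84 × (1 + 0.20 + 0.113) = 84 × 1.313 = 110.29, the printed 110.3. Rounded to equal arms, this is 112.

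No variant tried with 0.28 as a true d returns 110.3. At rho = 0.5, d = 0.28 needs 308 patients (power 85.1%) before any inflation.

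**Step 3. Power that 112 patients deliver.** Applying both losses in turn leaves 112 × 0.80 × 0.887 = 79.5 evaluable patients.

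| rho | Power at d = 0.28 | Power at eta-squared 0.069 |
|---|---|---|
| 0 (extreme) | 57% | 99% |
| 0.3 | 39% | 91% |
| 0.5 | 33% | 83.5% |
| 0.7 | 28% | 76% |
| 0.8 | 26% | 73% |
| 1 (extreme) | 23% | 67% |

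If all 112 were evaluable, power at d = 0.28 and rho = 0.5 would be 44%.

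**Step 4. Number needed if d = 0.28 were the target (rho = 0.5).** 308 evaluable patients. The plan's additive inflation gives 308 × 1.313 = 404.4, or 406 in equal arms. Dividing by 0.80 × 0.887 gives 434.0, or 436 in equal arms.

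**The case against.** **The 0.28 may be only a mislabelled f.** The f that belongs to eta-squared 0.069 is 0.272, close to 0.28. On that reading d = 0.28 was never a planning target, N = 112 agrees with the input that produced it, and the fault is one wrong symbol and the word for its size. Much of this stands. A reader might infer that the trial simply has 33% power instead of 85%, or that 112 patients are too few. The document does not support that: its own total reproduces from eta-squared 0.069 at just over 85%. The 33% holds only if d = 0.28 is taken literally.

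The explanation is not complete, however. 0.272 rounds to 0.27, and f = 0.28 at rho = 0.5 needs 80 patients, so 80 × 1.313 = 105.0, not 110.3. Where 0.28 came from stays open, and the source cited for it cannot be consulted here. The sponsor has to say what was intended. Under the mislabelled-f reading, calling the effect small is still wrong.

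**The correlation is inferred.** True, and any single power figure needs its range. But the contradiction in Step 1 needs no correlation, and at d = 0.28 no correlation from 0 to 1 brings power above 57%.

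**How a null result would be read is conjecture.** Fair: the reader also sees eta-squared 0.069, and the Statistical methods section says that an effect size will be determined. The document does not show what an ethics committee was told. This limits the claim about consequences but does not reconcile the two printed numbers.

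**Such detail belongs in the SAP or the full protocol.** This does not apply. The point is that two printed values contradict each other, not that something was left out.

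**Conclusion.** The point holds as an inconsistency in the stated effect size. Eta-squared 0.069 and d = 0.28 cannot describe the same difference between two equal arms. The sample size rests on the former, so the trial is sized for d of about 0.54: 85.5% power at 84 evaluable patients, about 83.5% at the 79.5 expected after both losses.

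Read as printed, d = 0.28 has about 33% power at correlation 0.5, 26% to 39% for correlations from 0.8 to 0.3, and 23% to 57% at the extremes. None is near 85%.

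The conversion rests only on two equal arms. The power figures also rest on the G*Power between-factors test and on rho, for which 0.5 is supported only because it returns 110.3. It does not follow that N is wrong for the effect it was derived from, nor that the sponsor meant d = 0.28.

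**What to change.** First, the sponsor confirms from its G*Power record which effect size and which correlation were entered. Then, in Sample size {14}:

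- **If eta-squared 0.069 is confirmed:** describe the effect as medium, with eta-squared = 0.069, f = 0.27 and d = 0.54, in place of the small effect with d = 0.28. State the correlation. Add that the trial is not powered for d = 0.28 (power about 26% to 39% for correlations from 0.8 to 0.3), so a null result does not exclude a small effect.
- **If d = 0.28 was truly intended:** replace the 85% by the power that 112 patients deliver for it, about 33% at correlation 0.5, with the range.

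Either way this is a few words in one section. It needs no extra patients and no change to design or analysis. The only cost is that the stated detectable effect, or the stated power, becomes less favourable.
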